### Affect school and script analysis – a psycho-educational method

#### Studies I and II

The intervention comprises eight weekly sessions of a group with five to seven participants (‘affect school’) with two instructors followed by ten weekly individual sessions (‘script analysis’). Two psychotherapists and one physician are recruited as instructors for both studies. They were trained together to become instructors by the constructors of the ASSA method, and have been instructors together in several ASSA groups. The same two instructors participate in all eight group sessions, which render three possible combinations: physician and psychotherapist I; physician and psychotherapist II; and psychotherapist I and psychotherapist II. The patients could be considered clustered within the pair of instructors. Patients will also be clustered by the set of five to seven participants included in each group. As depression is the main outcome measure we will test associations between depression symptoms, instructors and groups. Only one room will be used for all group sessions in each study.

At each affect school session a specific information handout is distributed, containing affect and script theory and the topics for the affect discussion. The scheme for the affect school sessions is presented in Table 1. During the first part of each affect school session the participants are instructed on general affect theory, and specific theory regarding the particular innate affects that are the topics for the session, followed by script theory. During the second part, the affect discussion, participants are encouraged to tell single-event autobiographical memory narratives; this exercise is considered important in psychotherapy [51]. The goal of the affect school is to achieve increased emotional awareness and verbal expressiveness. The affect theory presented during the affect school group sessions is essential for the script analysis, and we consider that participation in at least five group sessions is necessary to obtain an understanding of the theory. Persons with lower participation rate will not be offered script analysis. The total participation rate in ASSA will be counted.

**Table 1 Tab1:** General programme for the eight affect school sessions

*Affect theory*	
General affect theory is presented at all sessions. Specific affect theory for innate affects is presented according to the following program for the eight sessions.	
1) Joy	
2) Fear	

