### Basic body awareness therapy – a physiotherapeutic mind-body therapy

#### Studies I and II

This comprises ten weekly sessions for a group of five to seven participants with one instructor responsible for all sessions. Three physiotherapists, with special BBAT education and clinical experience of being BBAT instructors are recruited for both group and individual sessions in both studies. Before intervention, the BBAT instructors meet and synchronize how they will perform the interventions. The patients are clustered by BBAT instructors. Patients will also be clustered by the set of five to seven participants included in each group. We will test associations between depression symptoms, instructors and group. Only one room will be used for all group sessions in each study. Breathing, grounding, stability in the central line, centring, flexibility and flow are features systematically trained at each session. Patients are encouraged to observe and accept the sensations and emotions that awaken during the treatment situations. Patients systematically train to discern and differentiate between thoughts, emotions and body sensations. Continuous training and repetition are fundamental parts of BBAT [36].

Patients are offered five individual sessions where they focus on their own particular difficulties.

To balance the two intervention methods patients participating in fewer than five group sessions will not be offered any individual sessions. The total participation rate will be counted.

Enhanced body awareness and a greater unity between body and self are important goals [33]. Body awareness is the subjective, phenomenological aspect of proprioception and interoception that enters conscious awareness, and is modifiable by mental processes including attention, interpretation, appraisal, beliefs, memories, conditioning, attitudes and affects [33]. Important in BBAT is breathing, which is regarded as a central connector between body and mind. Improved body and mind integration is achieved by noticing, discerning, and differentiating thoughts, emotions and body sensations [33].

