### Primary and secondary outcome measures

In both studies, the primary outcome measure is the change in depression symptoms. Secondary outcome measures are changes in alexithymia and anxiety symptoms and self-image measures; changes in HbA1c concentration and midnight salivary cortisol concentration; use of antidepressants, and incidence of diabetes complications and mortality.

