### Power calculations for sample size

The standard deviation was 2.8 for the individual changes of Hospital Anxiety and Depression Scale – depression subscale after our intervention with ASSA for patients with chronic benign pain (calculated from raw data) [32].

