#### Study I

If we assume that the standard deviation for the individual changes in Hospital Anxiety and Depression Scale – depression subscale in this study is 2.8, a change of 1.4 points represents half the standard deviation, which is considered indicative of clinically relevant changes in subjective symptoms [52]. Calculating a statistical power of 80 %, and assuming significance at the 0.05 level, 64 persons in each intervention arm are required at follow-up in a two-arm randomized controlled trial. Unfortunately we only recruited around 21 persons in each arm in Study I, rendering a power of 37 %.

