#### Study II

The Kruskal–Wallis test will be used for changes in non-normally distributed variables (psychological symptoms and midnight salivary cortisol concentration).

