One limitation to our studies is that we only use self-report instruments, not structured interviews. Another limitation is that not enough patients in the first part of our randomized controlled trial agreed to participate in the intervention, so randomizing into three arms (ASSA, BBAT and a no-intervention group) was impossible. We aim to recruit more patients in Study II, to be able to perform the three-arm randomized controlled trial.

We foresee recruitment difficulties. Patients have generally not previously been introduced to the idea that emotional factors might impact their disease; presumably neither ASSA nor BBAT are methods known to the patients. Patients may feel that it is stressful to talk about emotions in a group situation and therefore BBAT may be more easily accepted.

Another difficulty is that most patients are working or university students, which might make participation difficult, therefore the Swedish Social Insurance Agency will offer preventive sick-leave compensation for treatment session time. It is, however, not possible to offer preventive sick-leave compensation for nonparticipants.

The clustering within the pair of instructors in ASSA might affect the results, but this will be tested. The three ASSA instructors were trained together, and have previously been ASSA instructors together in all three possible combinations; this will probably minimize the effects of clustering. The three BBAT instructors all have special training and long experience, but have not been trained together; however, they will co-operate in synchronizing how they will perform the BBAT intervention. The results of the interventions might be influenced by the group members being randomized into each group and by study design. Previously, we have carefully selected patients who we thought could benefit from the ASSA intervention and would not disturb the group dynamics. In the current studies, no individual selection can be made by the instructors, owing to the study design. Previously, we have made contracts with the patients to do their very best to participate in all sessions. In the current studies, we have declared that they can stop participating at any time.

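### Clustering by therapy group and instructor is acknowledged but only tested for, while the primary test and the Study II sample size assume independent patients

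*Protocol article*

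**What the plan says.** The sections on the two interventions describe two levels of clustering in both active arms: by instructor (one of three ASSA instructor pairs, one of three BBAT physiotherapists) and by therapy group. On the second level both sections say: "Patients will also be clustered by the set of five to seven participants included in each group". Usual care in Study II has no such structure.

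The response is a test. The ASSA section says: "As depression is the main outcome measure we will test associations between depression symptoms, instructors and groups". The BBAT section says much the same. The Discussion returns to the ASSA instructors: "The clustering within the pair of instructors in ASSA might affect the results, but this will be tested". It then expects their joint training to keep the effect small. No section says what follows from a positive or a negative result.

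On the outcome: "In both studies, the primary outcome measure is the change in depression symptoms". Under Statistical analysis, Study II, the Kruskal–Wallis "test will be used for changes in non-normally distributed variables (psychological symptoms and midnight salivary cortisol concentration"). Study I names the same test, with the Wilcoxon signed rank test. The regressions named for both studies are on baseline characteristics, with no cluster term.

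The section on power uses an SD of 2.8, a difference of 1.4 points, 80 % power, 15 % extra for Kruskal–Wallis in Study II and 10 % extra for non-response.

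**The concern.** Patients who share a group and an instructor for weeks are likely to have correlated changes in depression score. Kruskal–Wallis takes each patient as independent. If the correlation is positive, the test understates the variability of the two active arms, and a few good or bad groups, or one instructor, can produce a nominally significant difference. The same omission in the sample size makes the effective number of patients smaller than the number counted.

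Testing for clustering does not repair this. With about 12 groups and three instructors or pairs per arm, the test has little power, so a non-significant result says little about whether clustering is small enough to disregard. The comparison at stake is the primary one.

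**Working it through.** **1. The plan's own figures.** Inputs: "The standard deviation was 2.8 for the individual changes of Hospital Anxiety and Depression Scale" (depression subscale); "a change of 1.4 points represents half the standard deviation"; "assuming significance at the 0.05 level". Sidedness is not stated; two-sided is assumed.

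- Study I: n = 2(1.960 + 0.842)² × (2.8/1.4)² = 62.8, so 63 by the normal formula and 64 by the t distribution (power 80.1 %). The article says 64.
- Study I as recruited: 1.4/(2.8√(2/21)) − 1.960 = −0.340, power 36.7 %. The article says 37 %.
- Study II: means 0, 0, 1.4 give Σ(μᵢ − μ̄)²/σ² = 1.307/7.84 = 0.1667. With 60 per arm the noncentrality is 10.0 and power is 80.8 % (59 per arm gives 80.1 %). Then 60 × 1.15 = 69. The article says 60, then 70.

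All reproduce with independent patients, so no clustering allowance is hidden in them.

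**2. Design effect.** DE = 1 + (m − 1) × ICC. With m = 6, the middle of five to seven, DE is 1.05, 1.10, 1.25 and 1.50 at ICC 0.01, 0.02, 0.05 and 0.10.

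**3. The planned test in Study II.** Simulation of the three-arm Kruskal–Wallis test: 70 per arm, normal outcomes with total SD 2.8, groups of 6 and three instructor clusters in each active arm, usual care unclustered, at least 20,000 runs per case. Power is for one active arm differing by 1.4, with the critical value reset so that the true level is 5 %. Ranges show the spread between independent runs.

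| Assumed ICC | Type I error | Power at a true 5 % level |
|---|---|---|
| none | 4.9 % | 85 % |
| group 0.01 | 5.4–5.5 % | 83 % |
| group 0.02 | 5.8–6.0 % | 83 % |
| group 0.05 | 7.4 % | 77–79 % |
| group 0.10 | 10.3–10.4 % | 73–74 % |
| instructor 0.01 | 7.1 % | 79–80 % |
| instructor 0.02 | 9.5–9.9 % | 73–75 % |
| instructor 0.05 | 17.4 % | 60 % |
| group 0.05 + instructor 0.02 | 12.5–12.8 % | 68 % |

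The instructor level does more harm at the same ICC, because each of three instructors or pairs covers about 70/3 ≈ 23 patients.

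With normal data the 15 % uplift is largely spare, which is why power starts at 85 %. If it is fully used up by non-normality, as the plan reckons, 70 patients count as 60. ANOVA power at 60/DE is then 79, 77, 71 and 62 % at group ICC 0.01, 0.02, 0.05 and 0.10. This is somewhat pessimistic, because it also deflates the unclustered usual-care arm.

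**4. The association test.** A one-way F test with k groups of m exceeds its critical value with probability P(F > F_crit/[1 + m·ICC/(1 − ICC)]).

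- Groups: k = 12, m = 6, F_crit(11, 60) = 1.952. At ICC 0.05 the divisor is 1 + 0.30/0.95 = 1.316, and P(F > 1.484) = 16 %. At ICC 0.10 it is 33 %.
- Instructors: k = 3, m = 23.3, F_crit(2, 67) = 3.134. At ICC 0.02 the divisor is 1.476, and P(F > 2.12) = 13 %.
- Study I has about 21/6 = 3.5 groups per arm. At group ICC 0.05 the detection rate is 9 to 10 %.

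**The case against.** The strongest reply is that no ICC is given, so neither an inflated error rate nor a power shortfall is established. This stands. A reader might infer that the type I error certainly exceeds 5 % by a material amount and that 80 % power is not delivered. The documents do not support that: at group ICC 0.01 the error is about 5.5 %, and with normal data Study II keeps at least 80 % power up to a group ICC of about 0.02.

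Nor does the text say that clustering will be ignored after a null test. It is silent on what follows, and a fuller plan may settle it. The fair criticism is narrower: the article itself fixes the test, the calculation and the check for clustering, and they do not fit together.

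A reader might also compute the power of ASSA against BBAT alone, with n = 70/1.15/DE, and find 74, 69 and 60 % at ICC 0.02, 0.05 and 0.10. That is not the power the article promises. Its 80 % is for the three-group test, and the pairwise figure is already 78 % without clustering.

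Finally, the ASSA instructors trained together, which may make the instructor ICC small. That is plausible but unquantified. It does not cover the BBAT instructors, who the Discussion says were not trained together, or the therapy groups.

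**Conclusion.** The concern holds in conditional form and should be resolved before Study II starts. The article names two levels of clustering in both active arms, then judges the primary outcome by a test that assumes independence and sizes the trial without a design effect. With any positive ICC the planned test is anti-conservative. In Study II the type I error runs from about 5.5 % to 10 % over group ICC 0.01 to 0.10, and is about 10 % at instructor ICC 0.02 alone. The 80 % power holds only if clustering is small: with normal data it is lost near a group ICC of 0.05 or an instructor ICC of 0.01 to 0.02.

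These sizes rest on assumed ICCs, groups of 6, normal outcomes and two-sided testing. The power claim concerns Study II only, since Study I already reports 37 % from under-recruitment. The type I error point applies to both: with 21 per arm, the same simulation gives 7.3 % at group ICC 0.05 and 10.3 % at 0.10.

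**What to change.** - For the between-arm comparison of change in the HADS depression subscale, prespecify a partially nested mixed model: random intercept for therapy group in ASSA and BBAT, usual-care patients as singletons, arm-specific variances, and small-sample degrees of freedom (Satterthwaite or Kenward–Roger). Use it whatever the association test shows, and report that test as description only.
- State how the instructor level is handled. Three instructors or pairs per arm are too few to estimate a variance well. If they are treated as fixed, limit the conclusion to these instructors.
- Restate Study II power for the three-group test next to the 70 per arm, over a group ICC of 0.01 to 0.10 and a small instructor ICC. Recruitment for Study II had not begun when the article was written, so the target can still be reconsidered. As a guide, 70 × 1.25 = 87.5, or 88 per active arm at group ICC 0.05.

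The cost is some extra analysis work and a less favourable stated power. No new data are needed, because the planned association tests already require group and instructor identity.

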## Trial status

Patients from the hospital outpatient clinic were recruited in 2009 with the final follow-up section expected to take place in 2016. Recruitment from primary care centres will start in 2016.

## Abbreviations

ASSA: affect school and script analysis
BBAT: basic body awareness therapy
CONSORT: Consolidated Standards of Reporting Trials
IFCC: International Federation of Clinical Chemistry
NGSP: National Glycohemoglobin Standardization Program
